### Objectives

The present study outlines the protocol for a longitudinal, multicenter single-arm study among health care professionals investigating the role of theory-based motivational and volitional predictors for healthy habit formation in daily life based on a mHealth intervention targeting physical activity, healthy nutrition and mindfulness behaviors (i.e., engaging in mindfulness techniques and relaxation exercises). The aim of this paper is to outline the study protocol including a detailed description of the mHealth intervention, the evaluation plan, and the study design. The main purpose of this trial is to understand the habit formation process for physical activity, nutrition and mindfulness behaviors and its predictors. As preliminary hypothesis (hypothesis 1 a-e), we expect to find positive changes from baseline to post assessments (i.e., 100 days post baseline) in: a) habit strength, b) motivational constructs (i.e., intention, outcome expectancies, self-efficacy), c) volitional constructs (i.e., action planning), d) health behavior (i.e., physical activity, nutrition, mindfulness behaviors) and e) health status (i.e., stress, back pain, well-being, physical and psychological health, body mass index). For the primary endpoint (habit strength over time) and to understand predictors of habit formation over time, we hypothesize that a) habit strength at post-assessment is predicted by baseline motivational and volitional constructs, controlling for baseline habit strength (hypothesis 2), b) that health behavior and c) health status at post assessment are predicted by motivational and volitional constructs as well as habit strength at baseline (hypotheses 3 and 4, respectively). Finally, we hypothesize that next-week habit strength will show positive associations with behavior-related motivational (5a) and volitional constructs over time (5b).

Additionally, we conduct a process evaluation by evaluating participants’ experiences and satisfaction with the app. For the process evaluation a mixed-methods approach will be applied involving questionnaires and structured interviews. The items addressed in this protocol paper are based on the 2013 Standard Protocol Items: Recommendations for Interventional Trials (SPIRIT) statement [[58]; see Additional file 1].

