### Evaluation design

A one-arm, multicenter mHealth interventional study will be performed. Participants complete all assessments in the app with the same assessment rhythm irrespective of when participants enroll in the study. Upon registration, participants can complete questions on socio-demographic variables, psycho-social determinants (e.g., intention, self-efficacy), physical activity, nutrition and mindfulness as well as health-related outcomes (e.g., back pain). Data will be collected across a 100-day period at four assessment points: baseline (booking date + 0), interim after 4 weeks (booking date + 28) and 8 weeks (booking date + 56) and post-intervention (booking date + 99). Additionally, 11 weekly assessments will be scheduled (booking date + 7, + 14, + 21, + 35, + 42, + 49, + 63, + 70, + 77, + 84, + 91). Participants will receive reminder emails for the baseline and post assessment four days after the respective assessment date (i.e., baseline reminder booking date + 4 days, post assessment booking date + 104 days). Reminders for the remaining assessments are incorporated into the app (via “open tasks”, see Description of the intervention for further information). Outcome data will be the same for all participants, whether they continue or discontinue/deviate from the intervention protocol. One week after the completion of the intervention, a structured interview is scheduled with volunteers to gain insights in participants’ experiences with the app (e.g., practicability, operability, acceptability). Due to economic reasons, the total set of items varies per assessment point. The Fig. 3 presents an overview of the enrolment schedule, the intervention, worksheets and assessments.

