#### Psychosocial determinants of behavior change and habit formation

The following psychosocial determinants are assessed for physical activity, nutrition, and mindfulness behavior. Participants indicate their responses on a six-point Likert scale ranging from 1 (not at all true), 2 (not true), 3 (rather untrue), 4 (rather true), 5 (true) to 6 (absolutely true), if not otherwise specified. The baseline (t0), and post (t14) assessments focus on motivational (i.e., intention, outcome expectancies, self-efficacy) and volitional constructs (i.e., action planning), as well as on habit strength for physical activity, nutrition and mindfulness behaviors. The weekly assessments (t1, t2, t3, t4, t5, t6, t7, t8, t9, t10, t11, t12, t13) put focus on the habit formation process (i.e., self-monitoring, emotional states, context stability, intention, outcome expectancies) for all behavioral domains. Mean values and standard deviations are calculated to build the scales for the psychosocial determinants.

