##### Automaticity

Automaticity is assessed with four items by means of the subscale Self-Report Behavioral Automaticity Index from the Self Report Habit Index (SRHI) [65, 66] at baseline and post assessments, and with two items at interim assessments (due to economic reasons). Following the stem “Physical activity/ Eating five portions fruit and vegetables/ Practicing mindfulness activities three times per week for ten minutes … is something” participants indicate on a five-point Likert scale ranging from 1 (do not agree) to 5 (totally agree) if they engage in the behaviors for example “automatically”. The SRHI has proven to be a reliable and valid instrument to measure habit strength for physical activity (α = 0.96) [66].

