### Statistical power

The required sample size for the primary outcome (automaticity over time) was estimated based on recently published recommendations [78]. The power estimation revealed that a level-2-sample size with at least *N* = 228 participants (i.e., number of required individuals, accounting for 30% sample attrition) and a level-1-sample size of at least *n* = 13 measurement points (i.e., number of repeated measurements) is required to detect medium-sized population effects of *f* = 0.40 [21, 79] with sufficient power (≥ 0.80).

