### Statistical analysis

Statistical analysis will be performed using SPSS Version 27 and conducted after completion of the data collection process. Interim analyses will not be performed. All primary outcome data will be screened for normal distribution by using the Shapiro–Wilk test. Data will be checked for outliers and missing data. Descriptive statistics will be run to explore the sample characteristics. Continuous variables will be presented as means and standard deviations, while categorical variables will be displayed by percentages of participants in each possible category. Intention-to-treat analyses will be conducted, given that drop-out rates are usually high in eHealth research [80], per protocol analysis are not feasible. Only data sets from participants who completed the baseline, post and 50% of the weekly assessments will be included in the analysis. To investigate difference between the sample of analysis and those who provided baseline data only, differences between baseline scores and a dichotomous attrition variable (i.e., 0 = not retained for analysis, 1 = retained) will be analyzed using χ^*2*^ and *t*-tests, followed by logistic regressions. To test for changes in habit strength, motivational (intention, self-efficacy, and outcome expectations), volitional constructs (action planning), health behaviors and health status from baseline to post assessments, analysis of variance with repeated measures and *t*-tests between subsequent measures will be run (hypothesis 1 a-e). To examine hypotheses 2–4, hierarchical multiple linear regression analyses will be conducted, with motivational, volitional and habit-related predictors at baseline to predict habit strength, health status and health behavior at post-assessment. To account for the hierarchically structure of data (i.e., repeated measurements nested within individuals) we plan to run two-level models with 13 assessment periods nested in participants (hypotheses 5 a-b, linear mixed models, LMM, [81]). LMM allows to test for simultaneous assessment of the effects of within-person variation in weekly assessments of behavior,habit strength and predictor variables (level 1) and between-person variables such as age, health status and other covaraites measured only once (level 2). Prior to running analyzes, the time parameters will be grand mean centered to minimize multicollinearity. Subsequently, various steps will be undertaken to determine appropriate model fit, as suggested by Field [81]. Once the model shows appropriate fit parameters, LMM can be conducted by selecting the Restricted Maximum Likelihood for estimation method [81]. In a model including all behavior-related cognitions and covariates simultaneously, motivational and volitional variables will be modeled at the between-person level (e.g., comparing persons with higher average versus lower average intentions) and the within-person level (e.g., assessments when intentions to engage in health behavior were higher-than-usual vs. lower-than-usual). Models will be run separately for each behavioral domain.

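### The power statement and the 13-period model for hypothesis 5 need repeated measurements of automaticity and action planning that the described schedule does not contain

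*Protocol article*

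**What the plan says.** **What the analysis requires.** Statistical power opens with "The required sample size for the primary outcome (automaticity over time) was estimated based on recently published recommendations" and concludes that at least "13 measurement points (i.e., number of repeated measurements) is required to detect medium-sized population effects of" f = 0.40, with 228 participants including 30% attrition and power of at least 0.80. Objectives states hypothesis 5: "next-week habit strength will show positive associations with behavior-related motivational (5a) and volitional constructs over time (5b"). For this, Statistical analysis says "we plan to run two-level models with 13 assessment periods nested in participants". It counts habit strength among the variables assessed weekly at level 1, and it models motivational and volitional variables both between and within persons.

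**What the measurement sections schedule.** Automaticity is asked with four items "at baseline and post assessments, and with two items at interim assessments (due to economic reasons"). Evaluation design defines the interim points as "interim after 4 weeks (booking date + 28) and 8 weeks (booking date + 56") and lists 11 further weekly assessments separately. Of the assessments t1 to t13, Psychosocial determinants of behavior change and habit formation says that they "put focus on the habit formation process (i.e., self-monitoring, emotional states, context stability, intention, outcome expectancies) for all behavioral domains". The constructs of hypothesis 5b appear in the same section under another heading: "The baseline (t0), and post (t14) assessments focus on motivational (i.e., intention, outcome expectancies, self-efficacy) and volitional constructs (i.e., action planning"). The planning items at weeks 4 and 8 (Process evaluation) ask about using the app, not about physical activity, nutrition or mindfulness.

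**The concern.** A model of next-week habit strength over 13 periods needs the outcome in each period. A within-person volitional effect needs the volitional construct measured repeatedly. The measurement sections provide neither. The only sample-size justification in the article is for automaticity over time and makes 13 points a requirement, so it describes a design that the questionnaires do not implement. A mixed model tolerates missed questionnaires, but it cannot recover an outcome that was never asked. If the mismatch is found only after data collection, the waves, the outcome scale and the volitional predictor will have to be chosen with the data in hand.

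**Working it through.** **1. The plan's own figure.** Only the attrition step can be traced: 159 / 0.70 = 227.1, or 175 × 1.30 = 227.5, each rounding up to 228. The base number cannot be rebuilt, because alpha, the intraclass correlation (ICC), the number of predictors and the tested parameter are not given. That is not called an error here, since the figure rests on a cited recommendation. Retained participants: 228 × 0.70 = 159.6, about 160.

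**2. Occasions, from the days in Evaluation design.**

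| | Days | Count |
|---|---|---|
| All occasions (t0 to t14) | 0, 7, 14, …, 84, 91, 99 | 15 |
| t1 to t13 | 11 weekly, plus 28 and 56 | 13 |
| Automaticity | 0, 28, 56, 99 | 4 |
| Automaticity within t1 to t13 | 28, 56 | 2 |
| Action planning for the behaviours | 0, 99 | 2 |

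The five instruments described under Weekly assessments with regard to favorite exercises and tasks are self-monitoring, emotional state, context stability, intention and outcome expectancy. None measures automaticity or action planning.

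**3. One-step lagged pairs.** Fifteen occasions give 14 consecutive pairs.
- 5a (weekly intention or outcome expectancy, then automaticity at the next occasion): days 21 to 28, 49 to 56 and 91 to 99, so 3 pairs. Self-efficacy, the third motivational construct, is not weekly.
- 5b (action planning, then automaticity at the next occasion): 0 pairs.

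**4. Records with 160 retained.** Implied by 13 points: 160 × 13 = 2,080. Scheduled: 160 × 4 = 640. Lagged pairs for 5a: 160 × 3 = 480. The last two are maxima: the retention rule (baseline, post and half of the weekly forms) can be met by someone who skipped both interim assessments.

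**5. Effect on power: a range only.** Assume that 13 occasions give exactly 80% power at two-sided alpha 0.05, so the standardised effect is 1.960 + 0.842 = 2.802. Both are assumptions; the article says at least 0.80 and gives no alpha. Power at T occasions is Φ(2.802 × √r − 1.960), where r is the ratio of information.
- Within-person effect, information proportional to T − 1: r = 3/12 = 0.25 at T = 4, power 0.29. At T = 3, r = 2/12, power 0.21.
- Between-person effect, variance proportional to ICC + (1 − ICC)/T, at T = 4. For ICC 0.1, r = 0.169/0.325 = 0.52, power 0.53. For ICC 0.5, r = 0.538/0.625 = 0.86, power 0.74. For ICC 0.9, power 0.79.
- Linear time trend, information proportional to the spread of the occasions in weeks: r = 109.2/182.0 = 0.60, power 0.58.
- If instead f = 0.40 is read as a level-1 partial f² of 0.16 with 160 people, power exceeds 99% at T = 4 and at T = 3.

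**The case against.** **The schedule figure may say otherwise.** Evaluation design refers to Fig. 3, which was not available. If interim in the Automaticity section loosely meant every assessment between baseline and post, t1 to t13 would supply exactly 13 points. However, Evaluation design and Process evaluation both place interim at weeks 4 and 8, and no weekly instrument described measures automaticity. If the figure did show weekly automaticity, it would conflict with the text, and reconciliation would still be needed. What stands is that the count of four rests on the text alone.

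**The t1 to t13 list is not closed.** It covers days 28 and 56 yet omits automaticity, which is asked then. Its silence alone therefore proves nothing; the conclusion rests on the Automaticity section, the definition of interim and the weekly instruments taken together.

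**Self-monitoring is weekly.** Table 1 places it in the volitional stage, so a reader who infers that no weekly volitional measure exists goes too far. But Objectives, Psychosocial determinants and Statistical analysis all name action planning as the volitional construct, the weekly item counts days on which favourites were practised, and the outcome would still have four waves.

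**Stronger readings.** A reader might infer that the primary analysis as a whole fails. It does not: Objectives ties the primary-endpoint sentence to hypotheses 2 to 4 and adds hypothesis 5 afterwards, and hypotheses 1a and 2 need automaticity only at baseline and post, where all four items are asked. Nor is 5a impossible to fit; it has fewer occasions. A reader might also take one of the power values above as the trial's true power. The document supports none of them singly, because it does not state which effect is tested or the ICC. Finally, Statistical power ties 13 points to automaticity only; the need for repeated volitional measurement comes from hypothesis 5b and the within-person modelling.

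**Conclusion.** Wrong as written. On the schedule that the text describes, the condition attached to the stated power (at least 13 measurements of automaticity) is not met, and the 13-period model for hypothesis 5 cannot be run as specified. Automaticity has four occasions, with four items at two of them and two items at the others, so the waves are not on an identical scale. Hypothesis 5a survives in reduced form, and 5b with action planning has no week-to-week variation to analyse. The size of the power loss is open, from negligible to severe, and no single figure should be quoted. The conclusion assumes that interim has the meaning given in Evaluation design and that the schedule figure agrees with the text.

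**What to change.** Reconcile Objectives, Evaluation design, Psychosocial determinants, Automaticity, Statistical power and Statistical analysis, in one of two ways.

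1. **Restate for the scheduled waves.** Write hypothesis 5 and the mixed model for four automaticity waves, scored on the same two items at all four (assuming that the interim items are among the four). Enter action planning as a between-person baseline predictor. Alternatively, pre-specify self-monitoring as the weekly volitional predictor and acknowledge that its item counts days practised. Replace the power statement with the power or detectable effect for about 160 retained participants and four waves, naming the tested effect, alpha and assumed ICC.
2. **Add the measurements.** If the sponsor accepts the burden, put the same short automaticity items, and action planning for 5b, on the weekly forms so that the 13-period model exists. This runs against the article's stated economy of items and its own worry about attrition from many assessments, so it is a trade-off and not clearly the better choice.

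The first option costs text changes, a registry amendment and probably a less favourable power figure. The second adds changes to the app questionnaires and to participants' weekly load.

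### The hypothesis 5 mixed model states neither the one-week lag nor adjustment for current habit strength, so habit carry-over may be read as prediction

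*Protocol article*

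**What the plan says.** In the Objectives, hypothesis 5 has a time order: "next-week habit strength will show positive associations with behavior-related motivational (5a) and volitional constructs over time (5b"). For the baseline-to-post regression the same paragraph adjusts for the earlier level of the outcome: "controlling for baseline habit strength (hypothesis 2").

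The Statistical analysis section assigns hypothesis 5 to linear mixed models: "we plan to run two-level models with 13 assessment periods nested in participants". Level 1 covers "within-person variation in weekly assessments of behavior,habit strength and predictor variables (level 1"). Level 2 covers "between-person variables such as age, health status and other covaraites measured only once (level 2"). The motivational and volitional variables are split into a between-person and a within-person part, the latter illustrated by "assessments when intentions to engage in health behavior were higher-than-usual vs. lower-than-usual". Time centring, the estimation method and separate models per behavioural domain are also given. A shift of the outcome by one week is not mentioned, and habit strength at the predictor's assessment is not named as a covariate.

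The measurement sections bear on this too. The Automaticity section places the habit items at baseline, post and interim assessments. The introduction to the psychosocial determinants lists the content of the weekly assessments, and neither automaticity nor action planning is in that list.

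**The concern.** The hypothesis and its model do not match as written. The hypothesis looks one week ahead, but the model description does not say when the outcome is measured relative to the predictor. There are two ways to complete the description, and each has its own problem.

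- If predictor and outcome come from the same assessment, the model estimates a same-week association and does not address hypothesis 5.
- If the outcome is lagged but current habit is left out, the intention slope can absorb habit persistence. A person whose habit is above their usual level this week may also report above-usual intention, and will tend to have above-usual habit next week whether or not intention does anything.

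The Statistical power section names automaticity over time as the primary outcome, and the Discussion promises to examine whether changes in psychosocial variables predict changes in habit strength. With a single arm there is no control group to help with direction, so the time order and the adjustment for the earlier level carry most of the weight.

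**Working it through.** The plan gives no figure on this point, so there is none to reproduce. The check is a simulation with a known answer.

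**Inputs from the protocol.** N = 228 allowing for 30% attrition (Statistical power), so 228 × 0.7 = 159.6, taken as 160 people; 13 assessment periods (Statistical analysis).

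**Assumptions.** Two-sided 5% test; habit carry-over φ from 0 to 0.8; same-week within-person correlation r between intention and habit from 0 to 0.5. The protocol states none of these.

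**Model, unit variances.** Habit: h(t+1) = φ·h(t) + noise. Intention: x(t) = r·h(t) + noise. Given h(t), intention has no effect on h(t+1).

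**Expected slope.** In a long series, the slope of h(t+1) on x(t) without h(t) is cov[x(t), h(t+1)] = r·φ. For φ = 0.4 and r = 0.3 that is 0.3 × 0.4 = 0.12. Person-mean centring over 12 pairs of weeks pulls it down, so the simulated values are smaller. With φ = 0 the centring alone gives −r/n for n pairs: −0.3/12 = −0.025 with 13 waves and −0.3/3 = −0.10 with four.

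**Results for 13 weekly habit measures** (500 runs per cell, lagged model without current habit):

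| φ | r | mean slope (target 0) | rejection |
|---|---|---|---|
| 0.2 | 0.3 | 0.026 | 20% |
| 0.4 | 0.1 | 0.024 | 20% |
| 0.4 | 0.3 | 0.074 | 91% |
| 0.6 | 0.1 | 0.035 | 39% |
| 0.6 | 0.3 | 0.109 | 100% |
| 0.8 | 0.3 | 0.105 | 100% |

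With r = 0 rejection stays at 4% to 5% for every φ. With φ = 0 the slope is zero or slightly negative.

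- **Same-week model:** rejects in 91% to 100% of runs once r is 0.1 or more, so it carries no information on next-week prediction.
- **Lagged model with current habit:** slope between −0.002 and 0.002, rejection 3% to 6% in every cell.
- **Measurement error:** when habit is measured with error, adjustment is incomplete. In a separate simulation with such error, rejection with current habit in the model still reached 61% at φ = 0.7 and correlation 0.4. That figure depends on the assumed amount of error.

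**If habit exists at only four time points.** The Evaluation design section puts baseline, the two interims and post at days 0, 28, 56 and 99, so the gaps are 28, 28 and 99 − 56 = 43 days. None is a week. In the simulation with four equally spaced points, the lagged model without current habit was significantly positive in at most about 10% of runs and was often biased downward at low carry-over (φ = 0, r = 0.3: slope −0.102, rejection 47%, never in the positive direction). The table therefore applies only if habit strength is measured weekly.

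**The case against.** Four arguments can be made on the other side.

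1. *The quoted contrast only splits the predictor.* This is correct. A reader might infer that the plan compares same-assessment values, but the text does not say when the outcome is measured, and the Objectives give the lag. What stands is that the model description does not carry the lag over.
2. *Nothing excludes current habit.* Also correct. The covariate list is open, and habit strength appears at level 1 without a stated role. A reader might infer that the plan leaves it out, but the documents support only that it is not stated. This is a condensed article, and an analysis plan may say more. Even so, the description is fairly detailed, and the article does name the corresponding adjustment for hypothesis 2.
3. *Hypothesis 5 claims association, not effect.* In the simulation a lagged association does exist, so rejecting a null of no association would be right. The term false positive here refers to prediction beyond current habit. The Objectives place hypothesis 5 under understanding predictors of habit formation, and the Discussion speaks of prediction, so that stricter reading is the one that results will be given.
4. *The data may not be weekly.* This is the strongest objection, and it stands in part. The Automaticity section and the weekly item list point to four habit time points, while Statistical power and Statistical analysis imply 13 measurement points and weekly habit strength. The schedule figure is not available here. The size of the problem and the feasibility of the remedy both depend on this.

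**Conclusion.** The point holds in limited form and should be settled before analysis. The hypothesis 5 model states neither the lag nor adjustment for current habit strength. Without the lag it does not test the hypothesis. With the lag but without current habit, carry-over may pass for prediction.

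The size is conditional on weekly habit measurement, about 160 people retained, and both carry-over and same-week correlation above zero. Under those assumptions the false-positive rate runs from about 20% (0.4 and 0.1) to over 90% (0.4 and 0.3), against 3% to 6% with adjustment. A reader might conclude that a spurious effect is certain. The documents do not support that, because they give neither quantity, and with either at zero there is no spurious positive effect. Only intention was simulated. The same reasoning extends to 5b only if a volitional construct is measured at the same weekly waves.

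**What to change.** First reconcile the measurement sections (weekly item list without automaticity; automaticity at baseline, interim and post) with Statistical power and Statistical analysis (13 measurement points, weekly habit strength). Restrict hypothesis 5 to constructs and waves actually measured. This matters particularly for 5b, since action planning, the volitional construct named in the Objectives, is not in the weekly list.

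Then state the model: habit strength at the next assessment, regressed on person-mean-centred predictors at the current assessment, their person means, time, and current habit strength. Report it with and without current habit strength, and base any wording about prediction on the adjusted model.

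If habit is measured weekly, the cost is a sentence or two and one covariate. If it is not, the adjusted weekly model cannot be fitted, and the hypothesis must be reworded to the intervals available. Downsides: one wave is lost to the lag; the coefficient of lagged habit is itself biased in short series (the predictor slope was not, in the settings simulated without measurement error); and measurement error in habit, for which the protocol gives no reliability for the two-item version, leaves some carry-over in the predictor slope.
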